### 12.2.14 Local Tolerability

For patients randomized into arm A, local tolerability will be assessed. The following parameters will be evaluated:

- pain
- erythema
- swelling
- induration

### 12.2.15 Concomitant treatment

Drugs that are considered necessary for the patient's welfare may be given at the discretion of the Investigator. However, all of the concomitant medications need to be recorded in the e-CRF (see also Prior and Concomitant Therapy 10.8.).

### 12.2.16 Quality of Life Questionnaires

QoL will be assessed with the EORTC Quality of Life Questionnaire (QLQ-C30) version 3, the CML24 module.

QoL questionnaires must be filled out at the hospital/practice when the patient comes for a scheduled visit. The questionnaires will be handed out to the patients by the investigator or a study nurse prior to seeing the doctor for clinical evaluations. Patients will be asked to fill out the questionnaires as completely and accurately as possible. The average time to complete the entire questionnaire is approximately 10-15 minutes. QoL should be assessed at time-points indicated in 12.1 and Table 1 and Table 2.

### 12.2.17 Patient Diary

At Baseline Visit patients will receive a "patient diary form" to document the self-administration of study medication, toxicities/AEs and new concomitant medication. These sheets will be used by the treating doctor for documentation in the patient charts as data source for the e-CRF.

## 13 Discontinuation criteria

### 13.1 Withdrawal of patients from study treatment

All patients have the right to withdraw from the study at any time, for any reason, and without penalty or loss of benefits to which the patient is otherwise entitled. If the patient chooses to withdraw, the investigator must be informed immediately.

In case of premature end of the individual study therapy upon request of the patient, all efforts should be made to keep the patient in the study for follow-up. This is only possible if the subject will be informed verbally on the medically preferred option to still continue with the study surveillance procedures. The patient will then give his/her informed consent by means of a written, signed and dated consent form for the follow-up period. **The study visit(s) will then be continued according to protocol until the regular end of study (intention to treat).**

Reasons to prematurely discontinue study treatment in arm A or treatment free surveillance in comparator arm B **may** also be terminated by the investigator for one of the following reasons:

- Intolerable AEs / side effects of the study medication
- Severe (S)AE which make it necessary to stop study treatment permanently
- Abnormal laboratory value(s) which make it necessary to stop study treatment
- Non-compliance with the study protocol

Study treatment **must be** terminated for one of the following reasons:

- Pregnancy
- Reaching the primary endpoint, which is defined as an increase of the BCR-ABL level to > 0.1% (IS) at any time, corresponding to loss of MMR at any time
- Withdrawal of patient's consent to study treatment
- Study treatment termination by the investigator

**In case of molecular relapse (loss of MMR) or withdrawal of informed consent TKI treatment must be resumed immediately in arms A or B, irrespective of the phase of study.**

If the investigator terminates the treatment of patient prematurely, he has to inform the patient about his decision and has to record the primary reason for withdrawal in the patient file and to document the end of treatment in the e-CRF. Final study evaluations will be done according to the EOT visit. If the patient caused the premature withdrawal, all data before termination may be used for final analysis please also refer to 12.1.5 Premature End-of-Treatment assessments.

### **13.2 Premature discontinuation of the study**

A possible premature discontinuation of a single center or of the study as a whole must be documented adequately with reasons being stated and information must have to be conveyed according to national requirements (e.g. EC, CA, local regulatory authorities).

#### **13.2.1 Single center**

The Coordinating Investigator together with KKS Marburg, the Competent Authority (CA; BfArM) and the Ethics Committee (EC) has the right to discontinue this study at any time for reasonable medical or administrative reasons in any single center. Possible reasons for termination of the study could be but are not limited to:

- Unsatisfactory enrolment with respect to quantity or quality
- Inaccurate or incomplete data collection
- Unexpected accumulation of SAE/AE
- Major failure to adhere to the study protocol

#### **13.2.2 Study as a whole**

The Coordinating Investigator together with KKS Marburg, the CA and the EC has the right to terminate this clinical study as a whole at any time for reasonable medical or administrative reasons. For example:

- Unexpected accumulation of SAE/AE
- Change of risk-benefit considerations

If the study is prematurely terminated or suspended for any reason, the Investigator/institution should promptly inform the EC, CA and study patient or patient's legal representative and should assure appropriate therapy and follow-up for the patients.

## **14 Safety**

### **14.1 Definition**

#### **14.1.1 Adverse Events**

An "adverse event" is defined as follows:

"Any untoward medical occurrence in a patient or clinical trial subject administered a medicinal product and which does not necessarily have a causal relationship with this treatment".

"An adverse event can therefore be any unfavorable and unintended sign (including an abnormal laboratory finding, for example), symptom or disease temporally associated with the use of a medicinal product, whether or not considered related to the medicinal product".

#### **14.1.2 Adverse Reaction (AR)**

An 'adverse reaction' is defined as follows:

---

 European Parliament and the Council, 2001: Directive 2001/20/EC. Article 2 (m).

 European Medicines Agency, 2006: ICH Topic E 2 A. Clinical Safety Data Management: Definitions and Standards for Expedited Reporting, Step 5. Section 2A.

'All untoward and unintended responses to an investigational medicinal product related to any dose administered'.

'The definition implies a reasonable possibility of a causal relationship between the event and the IMP. This means that there are facts (evidence) or arguments to suggest a causal relationship'.

#### **14.1.3 Unexpected Adverse Reaction (UAR)**

An unexpected 'adverse reaction' is defined as follows:

'An adverse reaction, the nature or severity of which is not consistent with the applicable product information (e.g. investigator's brochure for an unauthorized investigational product or summary of product characteristics for an authorized product)'.

#### **14.1.4 Serious Adverse Event (SAE) or Serious Adverse Reaction (SAR)**

A serious adverse event or serious adverse reaction is defined as follows:

'Any untoward medical occurrence or effect that at any dose:

- results in death,
- is life-threatening,
- requires hospitalization or prolongation of existing hospitalization,
- results in persistent or significant disability or incapacity,
- or is a congenital anomaly or birth defect'.

'NOTE: The term "life-threatening" in the definition of "serious" refers to an event in which the patient was at risk of death at the time of the event; it does not refer to an event which hypothetically might have caused death if it were more severe'.

The severity of an adverse reaction is largely determined by the outcome of the medical occurrence. An adverse reaction should only be termed "serious" if hospitalization did in fact take place as a result of it. As a rule, hospitalization is the admission to a hospital with at least one overnight stay.

The presentation of a patient in the emergency room (casualty center, health care center) alone without subsequent in-patient admission does not yet fulfill the criterion hospitalization. However, it should be proofed whether any of the other criteria mentioned above justifies an adverse reaction being classified as "serious" or at least "medically significant".

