| Blood and lymphatic system disorders            | very common : leukopenia, thrombocytopenia
common : pancytopenia, neutropenia, anaemia                                                                                                                                                                                                                                                                                                                   |
| Immune system disorders                         | uncommon : basedow's disease                                                                                                                                                                                                                                                                                                                                                                                       |
| Endocrine disorders                             | common : hypothyroidism, thyroiditis
uncommon : hyperthyroidism                                                                                                                                                                                                                                                                                                                                          |
| Metabolism and nutrition disorders              | common : decreased appetite
uncommon : hypertriglyceridaemia                                                                                                                                                                                                                                                                                                                                             |
| Psychiatric disorders                           | common : depression, insomnia, anxiety, mood altered, mood swings, listless
uncommon : acute stress disorder, hallucination, emotional distress, nervousness, apathy, nightmare, irritability
not known : suicide attempt, suicidal ideation, aggression, bipolar disorder, mania, confusional state
(Reported as adverse reactions during treatment with other interferon alpha products.) |

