**14.5 Documentation and reporting of Serious Adverse Events**

All serious adverse events (SAEs) have to be recorded on a study specific SAE form from the time the informed consent has been signed, until end of study (month 15) for arm B plus an additional safety visit for arm A (month 16). After that period of time, only serious adverse reactions (events related to study medication) have to be reported. The SAE form has to be completed in English. The Investigator must fax all serious adverse events (SAEs) **within 24 hours after awareness** of the event to:

KKS Marburg

Philipps-Universität Marburg

[name]

D-35043 Marburg

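### Section 14.1.4 contradicts itself on whether an adverse reaction needs a hospital admission to be serious, and uses an undefined class, medically significant, that has no expedited reporting route

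*Protocol*

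**What the plan says.** Section 14.1.4 of the Protocol has three parts that bear on this.

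- **The list.** An event is serious if it is fatal, if it puts the patient's life at risk, if it "requires hospitalization or prolongation of existing hospitalization", if it leaves the patient with lasting or marked disability, or if it is a birth defect. The items are joined by *or*, so any one suffices.
- **The restriction.** Below the list, an adverse reaction is to be called serious only "if hospitalization did in fact take place as a result of it". The sentence after it describes hospitalization as, in general, an admission with an overnight stay.
- **The emergency-room paragraph.** A visit without admission does not meet the hospitalization criterion. The investigator is to check whether another listed criterion "justifies an adverse reaction being classified as" serious, or at least medically significant.

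What follows from the classification is set elsewhere:

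- Section 14.4.1 leaves the judgement of seriousness to the reporting investigator.
- Section 14.5 says "All serious adverse events (SAEs) have to be recorded on a study specific SAE form" and requires a fax within 24 hours. This applies to month 15 in arm B and month 16 in arm A. After that, only serious adverse reactions are reportable.
- Section 14.1.5 makes seriousness a condition for a SUSAR, and 14.12 sets the SUSAR timelines.
- Section 14.2 requires all adverse events on the CRF, over the same period as 14.5.
- Section 14.11 names no adverse events of special interest.

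**The concern.** The same section gives the investigator two incompatible rules for one decision: any one of five criteria is enough, or a reaction needs an admission. The 24-hour report and SUSAR eligibility both depend on that decision, and so does the incidence of serious adverse events, which section 4.2 includes in a secondary endpoint. The restriction is worded for adverse *reactions*. These are the events that can become SUSARs and the only kind still reportable after month 15 or 16.

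The second difficulty is the class *medically significant*. Section 14 neither defines it nor attaches a reporting rule to it, so an investigator who uses it has no instruction beyond ordinary CRF recording.

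The point matters for this drug. Section 10.2 lists "suicide attempt, suicidal ideation, aggression" among reactions seen with other interferon alpha products. It also cites a notification to investigators of new events with a possible relation, among them suicide and acute myocardial infarction.

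**Working it through.** There is no figure to recompute. The check sets the three parts of 14.1.4 side by side for an adverse reaction and then follows each classification through section 14.

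**Step 1: is the reaction serious?**

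| Case | Five-criterion list | Restrictive sentence, literally | Emergency-room paragraph |
|---|---|---|---|
| Admitted overnight | Yes | Yes | Not addressed |
| Fatal, not admitted | Yes | No | Other criteria apply |
| Life-threatening, not admitted | Yes | No | Other criteria apply |
| Lasting disability, not admitted | Yes | No | Other criteria apply |
| Birth defect, no admission | Yes | No | Other criteria apply |
| Emergency-room visit only, no listed criterion met | No | No | May be called medically significant |

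Under the literal restriction, four of the five criteria (death, life threat, disability, birth defect) no longer suffice without admission. Under the list they do, and the emergency-room paragraph agrees with the list. The restriction is therefore inconsistent with the text on both sides of it.

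**Step 2: what follows from each classification?**

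| Requirement | Serious | Medically significant only |
|---|---|---|
| CRF record to month 15 (B) or 16 (A), 14.2 | Yes | Yes, as an adverse event |
| Fax within 24 hours, 14.5 | Yes | None stated |
| SUSAR if related and unexpected, 14.1.5 and 14.12 | Yes | Not eligible |
| New event after month 15 (B) or 16 (A), 14.5 | Reportable if related to study medication | None stated |

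Surveillance continues to month 25 (section 12.1.6). The interval in which a newly arising, merely medically significant reaction has neither a required record nor a required report is 25 − 16 = 9 months in arm A. The same interval in arm B is 25 − 15 = 10 months, but arm B receives no study medication. In arm A, AOP2014 is given for 15 months, so for patients who complete treatment the later interval concerns late-appearing reactions.

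**Step 3: an example.** Take a suicide attempt seen in the emergency room, with no admission and no risk of death at the time. It meets none of the five criteria and falls into the undefined class. Section 14.7 judges expectedness against the Investigator's Brochure, and suicide attempt appears in the Brochure table reproduced in 10.2. The main loss would therefore be the 24-hour report rather than SUSAR status. If the attempt did put the patient at risk of death, the note in 14.1.4 makes it life-threatening and so serious under the list.

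**The case against.** The strongest reply is that context defeats the literal reading. The formal definition is the list, which the protocol quotes from the European directive. The restrictive sentence is followed at once by a description of hospitalization, and the paragraph after that tells the investigator to consider the other criteria when there was no admission. The sentence was probably meant to explain the hospitalization criterion alone. This stands as an account of intent, but the sentence does not say so, and the investigator who judges seriousness has to apply it as written.

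Three stronger readings are tempting and should not be drawn:

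- *Fatal reactions without admission would escape SAE status.* A reader might infer this from the restrictive sentence alone. The list and the emergency-room paragraph say otherwise. Section 14.5 asks for extra information when a trial subject dies, and 14.12 sets a seven-day limit for fatal or life-threatening suspected unexpected serious reactions.
- *Medically significant events go unreported altogether.* Section 14.2 puts every adverse event on the CRF to month 15 or 16, section 16.7 analyses adverse events by treatment group, and the DSMC may review them under 17.2. What is missing is the expedited route, and any required record of new events after that window.
- *Every case without admission is diverted into the undefined class.* The text concerns emergency-room visits only and offers *serious* first.

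It is also fair to say that nothing in the protocol requires a sixth seriousness criterion, and that the Safety Manual described in 14.13 is not available here and may add procedures. A manual would not remove a contradiction in the protocol's own definition.

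**Conclusion.** The point holds as an internal contradiction in the definition of seriousness, together with an undefined class that has no expedited route. It should be corrected, because the definition governs every 24-hour and SUSAR decision and the correction is cheap. The list and the emergency-room paragraph limit the likely harm.

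The number of events affected cannot be derived from the protocol. In logical terms, four of five criteria are put in doubt by one sentence. In time, the missing record for new medically significant reactions runs for the last 9 months of arm A's 25-month study period. No efficacy analysis or power calculation is affected.

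The conclusion assumes that investigators work from the protocol text and that the Safety Manual and SAE form, neither of which is shown, do not already settle the matter.

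**What to change.** Make two changes in section 14.1.4.

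1. Reword the restrictive sentence so that actual admission decides only whether the hospitalization criterion is met, and state that the other four criteria apply independently of admission.
2. Reconcile *medically significant* with sections 14.5 and 14.12 in one of two ways. Either define it as a seriousness criterion that triggers SAE reporting and, where related and unexpected, SUSAR reporting; or delete the term, so that the only outcomes are serious and not serious.

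The Safety Manual and the SAE form should then be checked against the amended wording.

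The first change costs only amendment text. For the second, adding the criterion costs a few more SAE reports and a form field. Deleting the term adds no reporting burden, but it leaves events such as the emergency-room example as ordinary adverse events, so that choice should be made deliberately.

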#### **14.1.5 Suspected Unexpected Serious Adverse Reaction (SUSAR)**

A SUSAR is an adverse event which

- has a reasonable possibility of a causal relationship to an IMP,
- is serious; and

 European Parliament and the Council, 2001: Directive 2001/20/EC. Article 2 (n).

 European Commission, 2011: Detailed guidance on the collection, verification and presentation of adverse event/reaction reports arising from clinical trials on medicinal products for human use ('CT-3'). Section 7.2.1, No. 45

 European Parliament and the Council, 2001: Directive 2001/20/EC. Article 2 (p).

 European Parliament and the Council, 2001: Directive 2001/20/EC. Article 2 (o).

 International Conference of Harmonisation, 2001: ICH Harmonised Tripartite Guideline Clinical Safety Data Management: Definitions and standards for expedited reporting - E2A: Section 2 B.

 Cf. Bundesinstitut für Arzneimittel und Medizinprodukte (BfArM) und Paul-Ehrlich-Institut und Bundesinstitut für Impfstoffe und biomedizinische Arzneimittel, 2010: 6. Bekanntmachung zur Anzeige von Nebenwirkungen und Arzneimittelmisbrauch nach § 63b Absatz 1 bis 9 des Arzneimittelgesetzes (AMG) vom 19.1.2010. Page 8.

 Cf. Bundesinstitut für Arzneimittel und Medizinprodukte (BfArM) und Paul-Ehrlich-Institut und Bundesinstitut für Impfstoffe und biomedizinische Arzneimittel, 2010: 6. Bekanntmachung zur Anzeige von Nebenwirkungen und Arzneimittelmisbrauch nach § 63b Absatz 1 bis 9 des Arzneimittelgesetzes (AMG) vom 19.1.2010. Page 8.

- is unexpected.

Therefore a SUSAR is not consistent with the applicable product information (e.g. Investigator's Brochure (IB) for an unauthorized investigational medicinal product or Summary of Product Characteristics (SmPC) for an authorized medicinal product.

### 14.2 Documentation of Adverse Events

Adverse events have to be recorded on case report forms (CRF) from the time the informed consent has been signed, up until end of study (month 15) for arm B plus an additional safety visit for arm A (month 16).

### 14.3 Severity

Severity of AEs will be graded according to the 'National Cancer Institute - Common Terminology Criteria for Adverse Events' (CTCAE – Version-No.4.0).

### 14.4 Causality

The assessment as to whether there is a reasonable possibility of a causal relationship (between the AE and the administration of study medication/TKI) is made by the reporting investigator according to following categories:

| Causality term  | Assessment criteria                                                                                                                                                                                                                                                                                                                                                                                                                                                                                   |
|-----------------|-------------------------------------------------------------------------------------------------------------------------------------------------------------------------------------------------------------------------------------------------------------------------------------------------------------------------------------------------------------------------------------------------------------------------------------------------------------------------------------------------------|
| Certain  | 
 
• Event or laboratory test abnormality, with plausible time relationship to drug intake
 
• Cannot be explained by disease or other drugs
 
• Response to withdrawal plausible (pharmacologically, pathologically)
 
• Event definitive pharmacologically or phenomenologically (i.e. an objective and specific medical disorder or a recognized pharmacological phenomenon)
 
• Rechallenge satisfactory, if necessary
 
 |
| Probable | 
 
• Event or laboratory test abnormality, with reasonable time relationship to drug intake
 
• Unlikely to be attributed to disease or other drugs
 
• Response to withdrawal clinically reasonable
 
• Rechallenge not required
 
                                                                                                                                                                                                 |
| Possible | 
 
• Event or laboratory test abnormality, with reasonable time relationship to drug intake
 
• Could also be explained by disease or other drugs
 
• Information on drug withdrawal may be lacking or unclear
 
                                                                                                                                                                                                                           |

 See European Commission, 2011: Detailed guidance on the collection, verification and presentation of adverse event/reaction reports arising from clinical trials on medicinal products for human use ('CT-3'). Section 7.3, No. 56.

 The term 'severity' is used here to describe the intensity of a specific event.

 Cf. Uppsala Monitoring Centre. The Use of the WHO-UMC system for standardised case causality assessment. Internet publication: <http://who-umc.org/Graphics/24734.pdf> (access 9th January 2013)

|                       |                                                                                                                                                                                                                                                 |
|-----------------------|-------------------------------------------------------------------------------------------------------------------------------------------------------------------------------------------------------------------------------------------------|
| Unlikely       | 
 
• Event or laboratory test abnormality, with a time to drug intake that makes a relationship improbable (but not impossible)
 
• Disease or other drugs provide plausible explanations
 
 |
| Not related    | 
 
• No causal relationship
 
                                                                                                                                                                      |
| Unassessable   | 
 
• Cannot be judged because information is insufficient or contradictory
 
• Data cannot be supplemented or verified
 
• Report suggesting an adverse reaction
 
                   |
| Not applicable | 
 
• If any of causal relationship does not make sense (e. g. patient didn't receive any study medication prior to the start date of the event)
 
                                                  |

